### Statistical analyses

Statistical analyses will be performed with the STATA statistical software (release 8, STATA corp, College station, Tex, USA)

Standard statistical tests will be used to compare the baseline characteristics of the departments and patients.

The main analysis concerns the effect of the intervention on the number of dangerously high INRs. The analysis will be carried out using a mixed effect analysis of variance model, in which the effect linked to the period will be considered fixed and that linked to the prescription tool will be considered random [22].

Rosendaal's method will be used to analyse the number of patient-days with INR over the target [21].

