### Assessment of evaluation criteria

#### OAT overdose

The Netlab^® ^application allows biological laboratories to receive prescriptions and to return results. All of the INR results can be extracted from the Netlab^® ^database accompanied by information making it possible to identify the patient, the treatment and dose received, the prescribing doctor, the hospitalisation unit, the date the test was prescribed. Data about overdoses can therefore be collected systematically by regular database searches.

Furthermore, the storage of the information in a computerised tool will make it possible to determine previous doses and INR results each time a drug is prescribed.

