#### Number of INR measurements and predicted frequency of overdoses

During a six-month period (January to June 2004), 4 920 INRs were requested by the six departments which already routinely use the computerized physician order entry system. The frequency of overtreatment can approximately be estimated from the percentage of INR > 4.5 among INR >2. Among the 2620 INR > 2, 330 (12%) were higher than 4.5 (see Table 4). This frequency has been stable during these six months but differed considerably between departments (10% to 23%).

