#### Hypothesis about the efficacy of the intervention

The number of INR tests necessary for a six-month period, with an α risk of 5% and a power of 80%, for the comparison of two percentages by classical methods (untreated group half the size of the treated group), for a basal incidence of the judgement criterion of 12% are and for the following hypotheses on relative reduction of the risk (RRR) of overdose, are:

• RRR 30%: 2500

• RRR 40%: 1300

• RRR 50%: 800

• RRR 60%: 500

Carrying out approximately 5000 tests over six months will make it possible to detect an intervention effect of less than 30% in this period. The experimental design includes three six-month periods and should thus ensure adequate power.

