## Regulatory aspects

According to French policy, this study was exempt from medical ethics committee approval. The anti-coagulants being evaluated are prescribed as recommended by clinical studies validated within the GPEH. These recommendations are available on the hospital's Intranet and are thus accessible to all doctors. They conform to standard practices. Neither the patients nor the doctors will be randomised. The interventions are simply different means of giving valid information to physicians. Using funding from the PHRC (Hospital Clinical Research Program), we carried out two research studies related to this project. In the first (PHRC 95), an intervention aimed at modifying the way in which emergency department doctors handle ankle injuries, the study design was a randomised controlled study and the randomisation unit was the hospital [11]. In the second (PHRC 98), a computer-based decision-support system for the prevention of venous thromboses in orthopaedics, the experimental design was identical to that of our present study [12]. In both cases, the Ile de France branch of the Clinical Research Delegation considered that the project was exempt from medical ethics committee approval.

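### Patients are not randomised to tool periods, yet baseline data are used only in significance tests and no patient baseline value is named in the main model, so differences in patient mix may remain in the tool effect

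*Protocol article*

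**What the plan says.** - **Use of baseline data.** Protocol article, Statistical analyses: "Standard statistical tests will be used to compare the baseline characteristics of the departments and patients". No other use is stated.
- **Main model.** The same section specifies a "mixed effect analysis of variance model, in which the effect linked to the period will be considered fixed", with the tool effect taken as random. No patient characteristic is named. The Methods paragraph of the abstract says that patient and physician clustering will be taken into account, and the Statistical unit section allows for an optional analysis by prescriber.
- **Allocation.** Under Experimental design, three six-month phases each hold one two-month block per condition (no support, non-personalised, personalised), ordered by a Latin square. Regulatory aspects states: "Neither the patients nor the doctors will be randomised".
- **Data at hand.** Under OAT overdose, the stored information "will make it possible to determine previous doses and INR results each time a drug is prescribed". The drug (fluindione or warfarin) is part of the order itself.

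**The concern.** The tools are compared between groups of patients who happened to be in hospital in different months. A patient's INR before the first order in the trial is likely to predict later time above 4.5 whichever tool is on, and the drug ordered may too. If such features differ between tool blocks, a baseline test may or may not flag the difference, but the estimate is unchanged either way. The plan attaches no action to a significant result, and a non-significant one may only reflect low power. Both main aims (tools against no tool, and personalised against non-personalised) rest on this comparison.

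**Working it through.** **1. What the design and the named terms control**

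- Three phases of three blocks give nine blocks, so three per tool. Block-level differences in patient mix average over only three blocks for each tool.
- The Latin square balances tools over phase and over position within a phase. Its stated purpose is to limit a learning effect, not to balance patients.
- Recruitment from November 2004 to May 2006 covers three six-month phases. The two-month calendar slots of the middle phase occur once, so each falls under one tool only. Seasonal patient mix in those months is therefore not balanced across tools.
- The protocol uses the word period for both the six-month phase and the two-month block. If the fixed period effect is the phase, it cannot absorb differences between blocks within a phase. If it is the block, each block has a single tool and the tool effect cannot be separated from it.
- Clustering terms mainly deal with correlation. Physician terms may take up some differences between physicians, but not differences between one physician's patients in different blocks.

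**2. The plan's own sample size**

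Inputs, from the section on the hypothesis about efficacy: "with an α risk of 5% and a power of 80" per cent; "for a basal incidence of the judgement criterion of 12" per cent; "untreated group half the size of the treated group". The 12% comes from the section on the number of INR measurements: "Among the 2620 INR > 2, 330 (12%) were higher than 4.5" (330/2620 = 12.6%). Sidedness is not stated; two-sided fits best.

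With p0 = 0.12, p1 = 0.12 × (1 − RRR) and pooled p̄ = (p0 + 2p1)/3:

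n0 = [1.96 √(1.5 p̄(1 − p̄)) + 0.842 √(p0(1 − p0) + p1(1 − p1)/2)]² / (p0 − p1)², total = 3 n0.

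| RRR | Computed total | Stated |
|---|---|---|
| 30% | 2442 | 2500 |
| 40% | 1287 | 1300 |
| 50% | 768 | 800 |
| 60% | 495 | 500 |

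Rounded up to the next hundred, all four match. The formula assumes independent INRs and no covariates, so it neither supports nor refutes the point.

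**3. Bias (illustration)**

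Shift in the tool contrast = difference in a subgroup's share between tools × difference in overdose rate between subgroups. The planned effect at RRR 30% is 12.0 − 8.4 = 3.6 points. The only heterogeneity figure in the protocol is the spread between departments, 10% to 23% (13 points), used here only as a scale. All differences in share, and the 5-point rate difference, are assumed.

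- 10-point difference in share × 5 points = 0.5 points.
- 10-point difference in share × 13 points = 1.3 points.
- 5-point difference in share × 13 points = 0.65 points.
- Difference in share needed to mimic the whole planned effect at a 13-point rate difference: 3.6/13 = about 28 points.

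**4. Precision (illustration)**

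Power = Φ[(p0 − p1 − 1.96 s0)/s1]. At 2500 INRs split 833 : 1667:

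- s0 (pooled) = √(0.096 × 0.904 × (1/833.3 + 1/1666.7)) = 0.01250
- s1 (unpooled) = √(0.12 × 0.88/833.3 + 0.084 × 0.916/1666.7) = 0.01315
- Power = Φ[(0.036 − 0.0245)/0.01315] = Φ(0.875) = 0.809

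With s1 in both places, power is 0.782. The pooled version is the one consistent with the plan's sizes.

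Suppose a covariate with assumed correlation ρ multiplies the variance by 1 − ρ². Using s1 throughout, power at 2500 goes from 0.782 to 0.819 (ρ = 0.3), 0.848 (0.4) or 0.885 (0.5). For the whole study, 3 × 2620 = 7860 INRs above 2, power is already 0.998 at ρ = 0. A gain appears only if a design effect is assumed as well: with 3, power goes from 0.800 to 0.899 at ρ = 0.5; with 4, from 0.680 to 0.800. The protocol gives neither ρ nor a design effect, and 1 − ρ² is a linear-model result that does not carry over directly to a logistic model.

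**The case against.** The strongest objection is that this is a condensed article with no analysis plan shown, and that a covariate list is commonly left to that plan. This stands in part: the absence of a list does not prove that the final analysis is unadjusted. But the section is not silent. It assigns baseline data to significance tests and names the effects in the model, so the comment is on a stated method.

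Four stronger readings are tempting and are not supported.

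- **That case-mix differences do sit in the tool effect.** A reader might infer this from the lack of randomisation. The protocol reports the overdose frequency as stable over the six months examined, includes every anticoagulated patient in the participating departments, and rotates the tools. Imbalance is possible, not shown.
- **That the plan would declare periods comparable after non-significant tests.** No such rule is attached to the tests.
- **That the trial lacks power without adjustment.** Under the plan's independence assumption the full study is at 99.8%. Any shortfall depends on an assumed design effect. No calculation addresses personalised against non-personalised separately.
- **That anticoagulant use before admission is already on file.** The protocol describes stored in-hospital orders, doses and INRs. It describes no field for treatment before entry.

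It is also fair to object that a pre-order INR could serve as the first point of the linear interpolation behind the time-above-4.5 endpoint, and so be covariate and outcome at once. The fix has to deal with that.

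**Conclusion.** The point holds in a limited form. In a comparison where neither patients nor doctors are randomised, the plan tests baseline characteristics but names no patient baseline value in the main model. Chance or seasonal differences in patient mix across three blocks per tool may therefore remain in the tool effect. The case rests on possible confounding, not on power.

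The size cannot be computed from the protocol. The 0.5 to 1.3 points against a planned 3.6 show scale only and rest on an assumed 10-point imbalance and an assumed rate difference of 5 to 13 points. Any gain in precision rests wholly on an assumed ρ and design effect. The change is worth making because it is nearly free, not because a bias has been demonstrated.

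**What to change.** 1. Prespecify in the main model, as fixed patient-level covariates, (a) the last INR before the patient's first in-trial anticoagulant order, in bands with a none-recorded category, and (b) the drug ordered, fluindione or warfarin.
2. Add anticoagulant started in hospital versus already taken on entry only if the hospital databases record it.
3. Take these values once, before the first in-trial order. Do not use the INR or dose preceding later orders, which the tool may already have influenced.
4. For the time-above-4.5 analysis, start observation time after the covariate INR, so that it is not also part of the outcome.
5. Keep the baseline table as description, and report the result without patient covariates as a sensitivity analysis.

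**Cost.** A few sentences in the analysis section and two variables that the protocol indicates are retrievable. The downsides are small: a missing-value category is needed, and in a logistic model the adjusted effect is conditional on the covariates, so absolute rates by tool should be shown beside it.

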**Methods:**

The study is an alternating time series experiment with three 6 months periods, each one including every 2 months according to a Latin square scheme: a control period without any reminder, a period with the simple non personalized reminder, a period with personalized reminder. All patients hospitalized in departments using the computerized physician order entry system and ordered *fluindione *or *warfarin*, will be included in the study between November 2004 and May 2006.

Main outcome will be the proportion of overcoagulation, as expressed by the proportion of observation time with INR over 4.5, assuming INR change linearly. Secondary outcome is the incidence of major haemorrhagic events. Data will be collected thanks to Hospital Information Systems databases.

Data will be analyzed taking into account patient and physician clustering effect.

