### Intervention

To prescribe a drug using Dx-Care^®^, the doctor selects the required drug from an exhaustive list. This opens up a dialogue box in which the doctor types the dose, the frequency of intake and the mode of administration. From this window, it is possible to add a text comment or to consult particular protocols that have been defined by the departments.

It is planned to integrate two types of decision support systems into the computerised prescription program:

1) non-personalised active system: when the drug is selected a window automatically opens giving the prescribing the nomogram for the adjustment of OAT doses in the form of a table (see Tables 2 and 3).

2) personalised active system: when the drug is selected a window automatically opens suggesting a dose recommended according to the nomogram (taking into account the doses previously received by the patient and the patient's INR), together with a date for next INR control and an explication.

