### Definition of endpoints

#### Overanticoagulation

Proportion of patient observation time with INR results > 4.5, assuming linear change of INRs.

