#### Statistical unit

In this study, the main aims are to guide each prescription and to reduce the number of anti-coagulant overdoses: the simplest statistical unit to study is therefore the INR result. This unit will be used to calculate the sample size.

This choice is not, however, perfect and the efficacy results will be presented using other indicators of the quality control of anti-coagulant treatments:

Given the low incidence of major haemorrhagic accidents (not currently measured at the GPEH but probably below 1%), it is not possible in this study to estimate the number of subjects necessary to demonstrate an effect of intervention on the "haemorrhagic accident" endpoint. Recording haemorrhagic accidents will give the frequency of such accidents, which will then be used for realistic estimates of power and sample size if further studies are carried out.

In previous studies evaluating the efficacy of tools to aid the prescription of OAT, the unit considered was not always the same, taking into account the number of INR per patient and the time between INR measurements to greater or lesser extents. The most recent studies considered the number of patient-days according to the method described by Rosendaal [15,16,21]. This method can also be used to calculate the rate of haemorrhagic events as a function of the number of patient-days for a given range of INR values.

We may also carry out an analysis for each prescribing doctor given that the intervention targets doctors directly. This will involve adjusting the effect of the intervention to the fact that intra-physician variability is *a priori *lower than inter-physician variability.

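### The declared main outcome is the share of observed time above INR 4.5, but the main analysis is of the number of high INR results

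*Protocol article*

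**What the plan says.** The Methods paragraph of the abstract declares: "Main outcome will be the proportion of overcoagulation, as expressed by the proportion of observation time with INR over 4.5, assuming INR change linearly". Under Definition of endpoints, Overanticoagulation is given in the same form: "Proportion of patient observation time with INR results > 4.5, assuming linear change of INRs".

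The Statistical analyses section reads differently: "The main analysis concerns the effect of the intervention on the number of dangerously high INRs", using a mixed-effect analysis of variance. A separate closing sentence adds: "Rosendaal's method will be used to analyse the number of patient-days with INR over the target".

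The sample size rests on individual test results. Under Statistical unit: "the simplest statistical unit to study is therefore the INR result. This unit will be used to calculate the sample size". The article then qualifies this: "This choice is not, however, perfect and the efficacy results will be presented using other indicators". It mentions Rosendaal's patient-day method there as the approach of recent studies, but does not make it the main analysis.

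Under Intervention, the personalised tool suggests a dose "together with a date for next INR control and an explication". The non-personalised tool is described only as displaying the nomogram table.

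**The concern.** The article attaches the word main to two different quantities: a proportion of time in two places, and a number of test results in a third. An analyst could follow either and claim to have followed the protocol, and the choice could be made after the data are seen.

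The Rosendaal sentence does not settle the matter. It is not called the main analysis. It refers to a number of patient-days rather than a proportion. Its threshold is a target that the text shown does not define, where the endpoint uses 4.5.

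The two quantities are also not interchangeable here. One intervention proposes when the next INR is to be taken, so it may act on the sampling process that generates the test results as well as on the INR itself.

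**Working it through.** **1. The sections side by side**

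| Section | Quantity | Threshold | Called main? |
|---|---|---|---|
| Abstract, Methods | proportion of observed time | > 4.5 | yes |
| Overanticoagulation | proportion of observed time | > 4.5 | endpoint definition |
| Statistical unit and sample size | INR results | > 4.5 among results > 2 | unit for sizing |
| Statistical analyses, main analysis | number of high INR results | not stated | yes |
| Statistical analyses, Rosendaal | number of patient-days | the target | no |

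**2. What the stated sample sizes refer to**

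Inputs, from the two sample-size subsections on predicted frequency and efficacy: baseline p1 = 0.12 (printed for 330/2620 = 12.6%), α 5%, power 80%, untreated:treated 1:2, relative reduction R. Two-sided testing is assumed.

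With p2 = 0.12(1 − R), k = 2 and p̄ = (p1 + k·p2)/(1 + k), the untreated group needs

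n = [z(0.975)·√(p̄(1−p̄)(1+1/k)) + z(0.80)·√(p1(1−p1) + p2(1−p2)/k)]² / (p1−p2)², and the total is 3n.

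| R | n | 3n | Article |
|---|---|---|---|
| 30% | 814 | 2442 | 2500 |
| 40% | 429 | 1287 | 1300 |
| 50% | 256 | 768 | 800 |
| 60% | 165 | 495 | 500 |

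Each computed total, rounded up to the next hundred, gives the article's figure. The figures are thus sound as a comparison of two proportions of INR results. They give no power for a proportion of time. That would need at least a mean and SD of the patient-level proportion and a number of patients, and the article gives none of these.

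**3. How testing alone can move the result-based measures**

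Assume 12% of time is above 4.5 under every tool. Let f and g be the relative test rates while INR is not high and while it is high. Then

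share of results high = 0.12g / (0.12g + 0.88f), and the number of high results is proportional to 0.12g.

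| Assumed testing | Share of results high | Change from 12% |
|---|---|---|
| f = g (uniform change) | 12.0% | none |
| f = 0.75, g = 1 | 0.12/0.78 = 15.4% | +28% |
| f = 1.25, g = 1 | 0.12/1.22 = 9.8% | −18% |
| f = 1, g = 1.5 | 0.18/1.06 = 17.0% | +42% |

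The share depends only on the ratio of g to f, so a uniform change in frequency leaves it alone. The count follows g, so a uniform change does move it.

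An apparent benefit can also arise. Suppose high INRs are tested 1.5 times as often in control periods and the share there is 12%. True time is then 0.12/(0.12 + 0.88 × 1.5) = 8.3%. If a tool evens out the testing, the share falls to 8.3%, an apparent relative reduction of about 31% with no true change.

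**4. Does the declared outcome behave better?**

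A simulation used the same true INR paths throughout (assumed: 14-day stay, autocorrelated daily INR, true time above 4.5 of 10.9%) and changed only the testing schedule:

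| Days to next test: after non-high / after high | High results per patient | Share of results high | Interpolated time > 4.5 |
|---|---|---|---|
| 3 / 3 | 0.55 | 10.9% | 9.6% |
| 2 / 2 | 0.76 (+40%) | 10.9% | 10.0% |
| 3 / 1 | 0.97 (+78%) | 17.2% | 9.2% |
| 4 / 1 | 0.83 | 18.2% | 8.6% |

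Interpolated time moves far less than the count, and far less than the share once timing depends on the INR. It does still move: the largest gap in this table is 10.0% − 8.6% = 1.4 percentage points.

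**The case against.** The strongest reply is that this is loose wording in a condensed article. The sample-size section plans on percentages of INR results, so the word number may stand for a proportion, and the target may be shorthand for 4.5. The article itself concedes that the INR unit is imperfect and promises other indicators, and the time-based analysis is planned. This weakens any claim that a second threshold was intended: the reference to a target is an ambiguity and no more. It does not remove the contradiction, because even a proportion of results is not a proportion of time, and no section makes the time measure the main analysis.

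A second reply is that the bias is hypothetical. That stands. A reader might infer that the personalised tool does change testing and so biases the main result. The article says only that the tool suggests a date. It does not say that physicians follow it, or in which direction testing would shift.

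A reader might also infer that any change in testing frequency moves the share of high results, but only a change that differs between high and non-high INRs does so. Nor can the personalised versus non-personalised comparison be singled out as the most exposed. The nomogram tables shown by the simple reminder are not reproduced and may themselves give INR timing.

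Finally, the 12% used as a share of time is borrowed. In the article it is the share of results above 4.5 among results above 2; among all requested INRs it is 330/4920 = 6.7%.

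**Conclusion.** The contradiction is established by the text: the abstract and the endpoint definition declare a proportion of time above 4.5, and the main analysis is of a number of high test results. It should be resolved before analysis, because the main result depends on which section is followed.

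That the choice can matter follows from the personalised tool's proposing the next INR date. The size of the effect is not established. The 9.8% to 17.0% range rests on assumed test rates and a fixed 12% of time above 4.5, and the simulation rests on an assumed INR process. These figures show that testing alone could produce shifts comparable with the smallest listed reduction of 30%, in either direction. Two of the three single-rate scenarios raise the share, and so would hide a benefit rather than create one. They do not show that such a shift will occur in this trial.

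**What to change.** In Statistical analyses:

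- Name as the main analysis the per-patient proportion of observed time with INR > 4.5, by Rosendaal's linear interpolation, compared between tools.
- Replace the reference to the target in the Rosendaal sentence with > 4.5.
- Make the analysis of INR results secondary, express it as a proportion rather than a number, and report it with INR tests per patient-day by tool.

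In the sample-size section, state that the calculation uses INR results as an approximation and is not a power calculation for the time outcome.

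No new data are needed: the INR results come from the laboratory extract already planned, and the method is already named. There are two costs. The stated power no longer refers directly to the main analysis, and calling the unit an approximation does not supply the missing calculation. Interpolated time is also less sensitive to testing frequency but not immune to it, which is why tests per patient-day should be reported alongside.

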### Georges Pompidou European Hospital (GPEH)

#### Organisation of the information system at GPEH

The hospital information system currently collates prescriptions and results of biological tests and imaging procedures. Eight hundred computers, both laptops and fixed posts, are used to in care procedures (in care departments and medical offices).

The Dx-Care^® ^program is at the centre of care delivery. It is used by doctors and nurses:

• to prescribe laboratory examinations and imaging tests for a patient,

• to visualise the results of laboratory tests,

• to establish and to consult nursing schedules,

• to archive a structured observation,

• to prescribe drugs.

Dx-Care^® ^is integrated with other applications to allow circulation of information between departments, laboratories and the pharmacy. Prescriptions for laboratory tests are transmitted to the Netlab^® ^program which manages such tests (this program is used by all biochemistry, haemostasis and immunology laboratories, etc.) The laboratories return the results using this same program, which retransmits them to Dx-Care^®^. Furthermore, prescriptions of drugs are transmitted to the Phedra program, which is used by the pharmacy to manage prescriptions. The prescription is validated by the pharmacy and this validation is then transferred to Dx-Care^®^. The lab test prescription facility has been available in the hospital information system since 2000 and is used by all departments of the hospital. The drug prescription facility has been implemented later on, since January 2003, and its use is still increasing (currently by half of the hospital departments).

The hospital information system thus allows to install decision support systems that are activated whenever a prescription is issued and routinely to collect evaluation criteria of prescription practices. If possible and validated, the use of the hospital information system to evaluate care procedures will make it possible to collect data regularly, and routinely to assess methods for the improvement of care practices.

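### The analysis section words both INR analyses as numbers with no denominator, although the endpoint is a proportion of observation time and the sample size compares two percentages

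*Protocol article*

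**What the plan says.** All references are to the protocol article.

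- **Statistical analyses, main analysis.** "The main analysis concerns the effect of the intervention on the number of dangerously high INRs". The sentence on the model begins "The analysis will be carried out using a mixed effect analysis of variance model, in which the effect linked to the period will be considered"; it makes period a fixed effect and the prescription tool a random one. No denominator, offset or weight is named.
- **Statistical analyses, second INR analysis.** Rosendaal's method "will be used to analyse the number of patient-days with INR over the target". No model is named, and the sentence refers to the target, not to 4.5.
- **Abstract, Methods.** "Main outcome will be the proportion of overcoagulation, as expressed by the proportion of observation time with INR over 4.5, assuming INR change linearly".
- **Definition of endpoints, Overanticoagulation.** "Proportion of patient observation time with INR results > 4.5, assuming linear change of INRs".
- **Main aims.** The effect is to be judged on the frequency of overanticoagulation.
- **Statistical unit.** The single INR result is the unit for sizing.
- **Hypothesis about the efficacy of the intervention.** Two percentages are compared from a 12% baseline, "for the following hypotheses on relative reduction of the risk (RRR) of overdose" of 30% to 60%.
- **Organisation of the information system at GPEH.** On the drug prescription facility: "its use is still increasing (currently by half of the hospital departments".

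**The concern.** A number of high INRs, or of days above a threshold, depends on how many patients are treated, how long they stay and how often they are tested, as well as on the quality of dosing. An analysis of variance of such totals has no term for exposure, so those quantities become part of the tool comparison. Use of the order entry system is growing, and the study takes in whichever departments use it, so volume is unlikely to be constant over the nine two-month blocks.

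At stake are the precision of the comparison, possible bias if volume differs by tool, and whether the result can be set against the 30% to 60% relative reductions for which the study was sized.

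**Working it through.** **1. The plan's own sizing is a comparison of proportions.** Inputs from the hypothesis section: p1 = 0.12, p2 = 0.12 × (1 − RRR), 5% risk (taken as two-sided), 80% power, untreated to treated 1:2. With pooled p̄ = (p1 + 2·p2)/3,

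n(untreated) = [1.96·√(1.5·p̄(1−p̄)) + 0.842·√(p1(1−p1) + p2(1−p2)/2)]² / (p1−p2)², total = 3n.

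For RRR 30%: p2 = 0.084, p̄ = 0.096, n = 814, total 2442. For 40%, 50% and 60% the totals are 1287, 768 and 495. The article states 2500, 1300, 800 and 500, which are these figures rounded up to the next hundred. So the sizing is on percentages, with INR results as denominator.

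**2. What a literal block count would do.** The section on the number of INR measurements gives 2620 INRs above 2 in six months. Three equal blocks hold 2620/3 = 873 each, and 873 × 0.12 ≈ 105 are high. The volume changes below are assumed, because no block volumes are given.

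- No tool effect, tool block with 10/20/30% fewer INRs: 94/84/73 high INRs. The apparent reduction is 10/20/30% on counts and 0% on the proportion.
- True RRR 30%, tool block with 10/20/30% more INRs: 1 − 1.1 × 0.7 = 23%, 1 − 1.2 × 0.7 = 16%, 1 − 1.3 × 0.7 = 9% on counts, and 30% on the proportion.
- A volume rise of 1/0.7 − 1 = 43% would hide the 30% effect completely.

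**3. Random volume in the Latin square.** A 3×3 Latin-square analysis of variance was simulated with no tool effect, 873 INRs per block on average, a 12% rate and independent INRs.

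| Assumed block-volume CV | Rejection rate, counts | SD of tool/control ratio, counts | Same SD, proportions |
|---|---|---|---|
| 0% | 5.1% | 0.07 | 0.07 |
| 10% | 4.9% | 0.11 | 0.08 |
| 20% | 4.8% | 0.19 | 0.08 |
| 30% | 5.0% | 0.28 | 0.08 |

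Hand check for counts: SD ≈ √[(2/3)(CV² + 0.88/105)]. At CV 0 this is √(0.667 × 0.0084) = 0.075; at CV 20% it is √(0.667 × 0.0484) = 0.18. Type I error is preserved and precision is lost.

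**4. Trend.** Each tool occurs once in every six-month period and once in every position. Numbering the blocks 1 to 9, the numbers for each tool sum to (0 + 3 + 6) + (1 + 2 + 3) = 15. A linear rise in volume therefore adds equally to all three conditions.

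**5. When volume can differ by tool.**

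- *Stepwise entry of departments.* The order of the periods is in a figure that is not shown; assume ABC/BCA/CAB. A step of size x from block 6 onwards falls on blocks 6 (A), 7 (C), 8 (A) and 9 (B). The mean for A rises by 2x/3, and for B and C by x/3. With x = 30% (assumed), A/B = 1.20/1.10 = 1.09: 9% more high INRs in the control condition with no tool effect.
- *Testing frequency.* Under Intervention, the personalised tool also suggests when the next INR should be done. It can therefore change the number of INRs, and with it the number of high ones.

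**The case against.** The strongest reply is that the denominator is in the document, only not in this section. The endpoint definition and the abstract give it, and the sample size section moves from reducing the number of overdoses to comparing two percentages with the INR result as unit. On that reading the analysis of variance is of a yes/no outcome per INR, it compares proportions, and block volume drops out. The design also removes a linear trend, and model details may sit in an analysis plan that is not shown.

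Much of this stands, and it rules out several stronger conclusions that a reader might draw:

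- *Both INR analyses are analyses of variance.* The text assigns that model only to the high INRs; the patient-days have no model named.
- *Volume biases the comparison one for one.* That needs block totals as the response and volume that differs by tool. The text does not fix the first and the documents do not show the second.
- *The relative reduction could never be estimated.* The reductions are sizing hypotheses, and a difference in proportions together with the control proportion yields a relative reduction.
- *A definite loss of patient-level power.* The documents give no distribution of stay and no within-patient correlation from which to derive one.

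The reply does not remove the mismatch. The article itself names the response of the main analysis, and it is not the endpoint that it defines. The yes/no reading is possible but not stated. Even under that reading the denominator would be INR results, which the personalised tool can alter, and not observation time.

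**Conclusion.** The point holds as a mismatch between the stated analysis on one side and the endpoint and sizing on the other. It is worth correcting before the data are analysed. Under a literal count reading the main cost is precision: at an assumed 20% block-volume CV, a 30% reduction is about 0.30/0.19 = 1.6 standard deviations of the tool/control ratio on counts, against about 0.30/0.08 = 3.8 on proportions. Bias is conditional on volume or testing frequency differing by tool; the 9% figure illustrates it under an assumed order and an assumed 30% step.

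These figures rest on equal average blocks of 873 INRs above 2, a 12% rate, independent INRs and assumed volume variation. Clustering within patients and physicians would widen both SDs. The mismatch itself rests on none of these assumptions.

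**What to change.** In Statistical analyses, replace the two references to a number by the defined endpoint:

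1. **Main analysis.** Days with INR above 4.5 (Rosendaal interpolation) over observation days, analysed as a rate or proportion. One suitable form is a log-link model with log observation days as offset and overdispersed or cluster-robust errors. Keep the planned time term and the patient and physician clustering announced in the abstract. Observation time should be the main denominator because the personalised tool can change how many INRs are done.
2. **Supporting analysis.** Each INR result above 4.5, yes or no, in a binomial model. State which INRs form the denominator: among those above 2 the rate is 330/2620 = 12.6% (the article gives 12%), among all it is 330/4920 = 6.7%.
3. **Reporting.** Rate or risk ratios with 95% CI for each tool against control and for one tool against the other, so that 1 − ratio can be set beside the planned relative reductions.

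The cost is a few sentences. The section on assessment of OAT overdose says that all INR results can be extracted with patient, unit and date, so the inputs are at hand. The only downside is a slightly more complex model than an analysis of variance.
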